9.2.3 Assessment of other outcomes of interest  
Not applicable

9.2.4 Assessment of safety outcomes  
Not applicable (described under section **9.2.1. Assessment of primary outcome**)

9.2.5 Assessments in participants who prematurely stop the study  
See chapter **8.5 Data Collection and Follow-up for withdrawn participants**.

## 9.3 Procedures at each visit

All patients will be screened and enrolled by the PI (this applies for part 1 and part 2). All assessments will be done by qualified trial personnel as declared on the authorisation log. Visits can be performed +/- 1 d from the described timepoint with the exception of the first treatment visit, which can be performed +7 d from the baseline visit.

### Dose escalation (part 1)

9.3.1 Visit 1: Screening (between day -28 until day -1)  
All patients will be screened by the PI. Patients willing to sign the informed consent form will be informed orally and in writing in detail about the exact procedures, their rights and duties. They will especially be informed that some screening assessments need to be done in order to decide if eligibility criteria are met.

- Explanation of the trial (risk/benefit) to the patients (60-120 min). Patient information is handed out in writing.
- Checking of all in- and exclusion criteria (10 min)
- Evaluation of the patient's medical history (10 min)

If inclusion and exclusion criteria are met as far as can be ascertained so far, and if at least 24 h have passed since patient information was given, written informed consent is signed by the participant and the PI. Then the following baseline assessments are performed:

- Pregnancy test for female patients with childbearing potential (blood test hCG).

- Clinical assessment (including physical medical and neurological exam, height and weight).
- Vital signs
- MoCA (20 min)
- Full lab tests

If all inclusion and exclusion criteria are still met, the patient is included in the trial, otherwise a screening failure is declared.

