| Measurements and procedures:           | 
Monocentric clinical trial phase I conducted with ascending escalating doses with the option of treatment prolongation, followed by a dose consolidation part with weekly TLN infusions in patients affected by PD.
 
Examinations before first trial treatment:
 Medical history, Clinical Assessment, vital signs, routine blood analysis, pregnancy test (if indicated).
 Assessment of baseline symptoms and LCT, MDS-UPDRS, PDQ-39 and ESS. Assessment of patient's psychological and cognitive condition: BDI, SAS, NMSQuest and MoCA.
 
Examinations during treatment:
 Assessment of AE and SAE. Vital signs, MDS-UPDRS and SAS, NMSQuest. LEDD, routine blood analysis.
 
Examinations after last trial treatment:
 Assessment of AE and SAE. Clinical assessment and vital signs, routine blood analysis.
 Assessment of final symptoms by LCT, MDS-UPDRS, PDQ-39 ESS and LEDD. Assessment of patient's psychological and cognitive condition: BDI, SAS, NMSQuest and MoCA.
 |
| Study Product / Intervention:          | Talineuren (TLN)                                                                                                                                                                                                                                                                                                                                                                                                                                                                                                                                                                                                                                                                                                                                                                                                                                                                                                                                                                                                                              |

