## **2.7 Patient Information and Informed Consent**

This trial will not include vulnerable patients nor healthy volunteers. The investigators will explain to each candidate the nature of the trial, its purpose, the procedures involved, the expected duration, the potential risks and benefits and any discomfort it may entail. Each candidate will be informed that the participation in the trial is voluntary and that he/she may withdraw from the trial at any time and that withdrawal of consent will not affect his/her subsequent medical assistance and treatment.

The candidate must be informed that his/her medical records may be examined by authorised individuals other than their treating physician.

All potential participants for the trial will be provided with a participant information sheet and a consent form describing the trial and providing sufficient information for her/him to make an informed decision about their participation in the trial. They will have up to 28 days to decide if they wish to enter the trial or not.

The formal consent of a participant, using the approved consent form, will be obtained before the participant is submitted to any trial procedure. The patient will be informed about pre-screening assessments needed for the evaluation of the eligibility criteria prior to trial enrolment. Patients will thus know, that if pre-screening results do not meet eligibility criteria, they might not be enrolled to the trial. In that case, this will be judged as screening failure.

The participant should read and consider the statement before signing and dating the informed consent form, and should be given a copy of the patient information and informed consent. The consent form must also be signed and dated by the investigator (or his/her designee) at the same time (or before) as the participant signs, and it will be retained as part of the trial records.

After having completed the regular treatment schedule including the follow-up visit, all patients from part 1 (patient 1 to 3) will have the opportunity to continue receiving weekly TLN infusions for an additional 8 weeks according. All patients wishing to prolong their TLN treatment will be provided with an amended patient information and consent form describing the additional treatments and assessments. Written informed consent will be obtained before the participant is submitted to any amended trial procedure.

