| Pregnancy Test                | x         |          |               |        |        |        |        |   |    |    |    |    |    |    |                  |           |
| Medical History               | x         |          |               |        |        |        |        |   |    |    |    |    |    |    |                  |           |
| Clinical Assessment           | x         |          |               |        |        |        |        |   |    |    |    |    |    |    | x                | x         |
| Vital Signs                   | x         | x        | x             |        |        |        |        | x | x  | x  | x  | x  | x  | x  | x                | x         |
| MoCA                          | x         |          |               |        |        |        |        |   |    |    |    |    |    |    | x                |           |
| Lab tests                     | x         | x        |               |        |        |        |        | x | x  | x  | x  | x  | x  | x  | x                | x         |
| Levodopa Challenge Test       |           | x        |               |        |        |        |        |   |    |    |    |    |    |    | x                |           |
| TLN Infusion                  |           |          | x             |        |        |        |        | x | x  | x  | x  | x  | x  | x  |                  |           |
| Blood collection (PK)         |           |          | x             | x      | x      | x      | x      |   |    |    |    |    |    |    |                  |           |
| MDS-UPDRS                     |           |          | x             |        |        |        |        | x | x  | x  | x  | x  | x  | x  | x                | x         |
| PDQ-39                        |           | x        |               |        |        |        |        |   |    |    |    |    |    |    | x                |           |
| ESS                           |           | x        |               |        |        |        |        |   |    |    |    |    |    |    | x                |           |
| BDI                           |           | x        |               |        |        |        |        |   |    |    |    |    |    |    | x                |           |
| SAS                           |           | x        |               |        |        |        |        |   |    |    |    |    |    |    | x                |           |

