#### Schedule of assessment part 2:

In summary: Nine patients in total are foreseen to participate in part 2 of the trial. These 9 patients will all receive the MSD during 8 weeks. Between 28 days and one day before the start of the trial for them, patients will be screened if they qualify for the participation in the trial. If all eligibility criteria are fulfilled, patients will be enrolled to the trial and trial specific procedures will start. During week 1, patients have to show up every day at the CI Bern. CI Bern is a clinical trial unit providing facilities and services to support clinical trials and serves as satellite site. CI Bern was chosen in order to perform PK sampling and assessments. As of week 2, patients will only have one visit per week, where treatment (TLN infusion) and assessments will take place at the same time. These visits will take place in the Institute of Neurology in Konolfingen. All patients will continue in the same manner and receive a weekly infusion of TLN until criteria are met to stop the treatment.

Patients from the part 1 of the trial, wishing to take the option of continuing the treatment will follow the same schedule as the patients of part 2 (see schedule of assessment above) with the exception of the PK sampling, and baseline (the data will be added to part 1). All assessments will take place in the Institute of Neurology in Konolfingen.

| Trial Periods                 | Re-consent | T | T | T  | T  | T  | T  | T  | T  | Final assessment | Follow-up |
|-------------------------------|------------|---|---|----|----|----|----|----|----|------------------|-----------|
| Visit                         | 0          | 1 | 2 | 3  | 4  | 5  | 6  | 7  | 8  | 9                | 10        |
| Time (weeks)                  | -4 to -1   | 1 | 2 | 3  | 4  | 5  | 6  | 7  | 8  | +1               | +4        |
| Time (days)                   | -28 to 0   | 1 | 8 | 15 | 22 | 29 | 36 | 43 | 50 | +7               | +28       |
| Patient information & consent | x*         |   |   |    |    |    |    |    |    |                  |           |
| Clinical Assessment           |            |   |   |    |    |    |    |    |    | x                | x         |
| Vital Signs                   |            | x | x | x  | x  | x  | x  | x  | x  | x                | x         |
| MoCA                          |            |   |   |    |    |    |    |    |    | x                |           |

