## 9.2 Assessments of outcomes

### 9.2.1 Assessment of primary outcome

Clinical AEs, lab values and vital signs, will be assessed during each visit as reflected in the two schedules (part 1 and part 2 of the trial). In addition, patients will also be asked to contact the PI's practice if they experience any adverse effect between visits, to assess if this could be related to the treatment and would require further medical attention and if any actions are to be taken. Patients will be asked to provide as much detail as possible at the time of the visit. Details should include the time and duration of these occurrences that will be examined with the investigator to fill the weekly reporting of AE. The investigator will document the AEs in the eCRF after each visit and will notify the sponsor in case of SAEs. All AEs and SAEs will be documented as follows: time of onset, duration, resolution, action to be taken, assessment of intensity, relationship with trial treatment (for all details refer to section **10 SAFETY**). Pre-existing signs and symptoms, especially of PD, are not to be considered an AE. Parkinsonian signs and symptoms are considered an AE in this trial if they appear to be new or if a previously present non-fluctuating symptom clearly worsens. A fluctuating parkinsonian symptom will only be counted as an AE if the fluctuation clearly increases in frequency or duration or if the extent of the fluctuating symptom at its worst is clearly worse compared to the baseline condition.

In order to assess other safety issues, blood samples will be taken and analysed for routine assessments (termed full lab tests thereafter) to assess if TLN modifies the blood cell count, the electrolytes, metabolites and liver markers (for the full list of lab tests and standard values see the **Annexes 1 & 2**) or result in an elevation of anti-GM1 antibodies or apolipoprotein B (a marker of hyperlipidaemia).

The full lab tests consist of:

- 1- The "routine" lab analyses will be performed (Cat #: Rout-3549)
- 2- Anti-GM1 IgG antibodies (Cat #: gm1g 52250)
- 3- Apolipoprotein B (Cat #: apob-7320) assays

All required material will be provided by Viollier. 4 tubes (3 x 0.5 ml of blood serum-gel-tube and 1 x 0.5 ml of blood in EDTA tube) will be required for these tests from each patient.

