Safety lab values will be assessed from blood collection performed every week during part 1 (3 days after TLN infusion) and part 2 (on the day of TLN infusion) according to the schedule. Abnormal

values will be compared to the normal range provided by the laboratory (**Annex 2**), then assessed by the PI for grading. All analyses will be performed from venous blood collection before the infusion. Samples will be collected on each sampling day by courier by Viollier and processed in their facilities.

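### hCG is tested only at screening: the result can be 35 days old at the first infusion, and no test is listed before the optional extension restarts dosing

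*Protocol*

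**What the plan says.** Both visit lists place the test at Visit 1: "Pregnancy test for female patients with childbearing potential (blood test hCG" (Protocol 9.3.1 for Part 1; 9.3.7 repeats it for Part 2). The row "Pregnancy Test" in the Part 2 schedule table is marked in the screening column only. The synopsis names the test among the examinations before first treatment: "routine blood analysis, pregnancy test (if indicated".

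The laboratory panel does not supply it elsewhere. Section 9.2.1 defines the panel under "The full lab tests consist of" as the routine analyses, anti-GM1 IgG and apolipoprotein B, and Annex 1 lists no hCG. The lists for baseline, treatment, assessment, final and follow-up visits (9.3.2 to 9.3.6 and 9.3.8 to 9.3.13) contain no pregnancy test.

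On timing, screening runs from day -28 to day -1 and baseline is day 0. Section 9.3 allows a wider window for "the first treatment visit, which can be performed +7 d from the baseline visit". The extension is offered "After having completed the regular treatment schedule including the follow-up visit" (section 2.7). Section 9.1 says that its patients follow the Part 2 schedule "with the exception of the PK sampling, and baseline (the data will be added to part 1". The extension's own table and visit lists (9.3.14 to 9.3.17) start at re-consent and show no pregnancy test. The re-consent visit consists of explanation and written information, and drops out if consent is taken at a late Part 1 visit.

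**The concern.** Pregnancy is an exclusion criterion (7.1), a withdrawal criterion (7.3) and grounds for immediate withdrawal (10.1.1). These rules work only if a pregnancy is recognised. If contraception fails after screening, the visit schedule contains nothing that would detect it. Recognition then rests on the patient noticing and reporting, and a first course or a new course of up to eight infusions could begin in the meantime.

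TLN itself has no clinical data (3.4), and no GLP-compliant toxicity study was done with TLN as such (3.3.4). Experience with free GM1 is large, at 2658 patients in 51 trials (3.4.1). What is at stake is avoidable exposure in early pregnancy, not the analysis.

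**Working it through.** The Protocol states no figure for the age of the test, so there is none to reproduce. The check is day arithmetic.

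**Inputs**
- Screening day: -28 to -1 (9.3.1, 9.3.7).
- First infusion: nominal day 1, or day 7 if the +7 d window from the day 0 baseline is used (9.3).
- Part 1 doses: up to 14, weekly (8.1.1). Treatment visits 3, 5, ... 29 also give 14.
- Part 1 follow-up: 28 days after the last infusion (9.3.6).
- Extension: starts after that follow-up (2.7, 3.9). Its table allows re-consent from day -28 to day 0, with the first infusion on day 1.

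The general +/- 1 d visit window and treatment delays are ignored.

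**Age of the test at first infusion** = first infusion day - screening day
- Screening on day -28: 1 + 28 = 29 days nominal; 7 + 28 = 35 days at most.
- Screening on day -1: 1 + 1 = 2 days; 7 + 1 = 8 days.

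**Age at extension restart, 14 doses, restart on the follow-up day**
- Last infusion = first infusion day + 7 x 13: day 92 or day 98.
- Follow-up = last infusion + 28: day 120 or day 126.

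| Screening day | First infusion day 1 | First infusion day 7 |
|---|---|---|
| -28 | 120 + 28 = 148 days | 126 + 28 = 154 days |
| -1 | 120 + 1 = 121 days | 126 + 1 = 127 days |

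The range is therefore 121 to 154 days.

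**Later restart.** If re-consent at follow-up counts as day -28 of the extension and its first infusion is on day 1, restart comes 29 days later. For screening on day -28 this gives 148 + 29 = 177 days or 154 + 29 = 183 days.

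**Early stop.** Section 6.1.3 lets patients continue at their personal maximal suitable dose, so a patient who stopped before level 14 can still enter the extension. With five doses, the last infusion is on day 1 + 28 = 29 or 7 + 28 = 35, and follow-up on day 57 or 63. The test is then 57 + 28 = 85 or 63 + 28 = 91 days old (screening day -28), or 57 + 1 = 58 or 63 + 1 = 64 days old (screening day -1).

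The interval changes with the scenario, but in every case the only listed test precedes the whole first course and its 28-day follow-up.

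**The case against.** Much of the case against acting is sound. Women of childbearing potential must use double contraception, hormonal and mechanical, for the whole study. Section 10 runs trial duration to the last protocol procedure, including a 28-day safety follow-up, so a reader might infer that contraception lapses in the extension, but the text does not support that. Patients are aged 40 to 80, and women more than 2 years post-menopausal are not counted as of childbearing potential. There are 12 patients in all and at most 3 in the extension, so possibly no participant is affected. The visible text describes no reproductive hazard of GM1 or TLN, so none should be inferred.

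A reader might also take 148 to 154 days as the minimum gap at restart. It is not: it needs screening on day -28 and all 14 doses, and the working shows shorter gaps.

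Section 9.1 excepts only PK sampling and baseline when it refers extension patients to the Part 2 schedule, so one could argue that screening, with its test, carries over. The extension's own table and visit lists make this unlikely, since they begin at re-consent with no screening column.

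Finally, the Part 1 schedule table is illegible in the copy reviewed, and neither the safety management plan nor the extension consent form was visible. Either document could add a test. This limits certainty, but the legible visit lists for both parts and the extension agree with one another.

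**Conclusion.** The point stands as a minor safety improvement. As the visit lists are written, the only hCG result can be up to 35 days old at the first infusion, and no test is listed before the extension restarts dosing. There it is about 121 to 154 days old after a full escalation with restart on the follow-up day, up to about 183 days if the re-consent window is used, and about 58 to 91 days after five doses. These figures assume weekly dosing without delay.

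The gap concerns detection if contraception fails, in very few women. It would be wrong to read it as affecting the safety tables, the efficacy comparisons or any other statistical result. The point is also confined to the start of each course: testing between infusions within a course is a separate choice, which the change below does not address.

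**What to change.** For women of childbearing potential only:

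1. **First course.** Add hCG to the blood already drawn at Visit 2 in both parts (9.3.2, 9.3.8) and require a negative result before the first infusion. The +7 d window leaves time for the result and keeps it at most 7 days old.
2. **Extension.** Add hCG to the Part 1 follow-up draw (9.3.6) and require a recent negative result before the first extension infusion, for example no more than 7 days old. The exact limit is a judgement; the Protocol gives none. If restart is later, repeat the test, because the follow-up result could be 29 days old by then. The repeat must be drawn ahead of the dosing visit, since safety blood goes to an outside laboratory: "Samples will be collected on each sampling day by courier by Viollier and processed in their facilities".

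The cost is one extra assay before the first course and a second for a woman who enters the extension, on blood already scheduled unless restart is delayed. Sections 9.3.2, 9.3.6 and 9.3.8, the extension visit list and the schedule tables (which appear both at the front and in 9.1) need editing. Nominal first dosing is the day after baseline, so waiting for the result may move the first dose. In Part 2 that could mean rebooking the PK week at CI Bern, and in Part 1 it could shift the 1 + 2 stagger.

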9.3.2 Visit 2: Baseline (day 0)

- Vital signs
- Full lab tests
- LCT
- PDQ-39
- ESS
- BDI
- SAS
- NMSQuest
- LEDD

9.3.3 Visit 3, 5, 7, 9, 11 and every other visit until visit 29: Treatment

- Vital signs
- TLN Infusion
- MDS-UPDRS (Part III before the infusion; Part I, II and IV during the infusion; Part III again after the infusion)
- AE recording

9.3.4 Visit 4, 6, 8, 10, 12 and every other until visit 28: Assessment

- Vital signs
- Full lab test
- NMSQuest
- LEDD
- AE recording

9.3.5 Visit 30: Final assessment (7 days after last TLN infusion)

- Clinical assessment (including physical medical and neurological exam, height and weight).
- Vital signs
- MoCA
- Full lab test
- LCT
- MDS-UPDRS
- PDQ-39
- ESS
- BDI
- SAS
- NMSQuest
- LEDD
- AE recording

9.3.6 Visit 31: Follow-up (28 days after TLN infusion)

- Clinical assessment (including physical medical and neurological exam, height and weight).
- Vital signs
- Full lab test
- MDS-UPDRS
- LEDD
- AE recording

## **Dose consolidation (part 2)**

### **9.3.7 Visit 1: Screening (between day -28 until day -1)**

All patients will be screened by the PI. Patients willing to sign the informed consent form will be informed orally and in writing in detail about the exact procedures, their rights and duties. They will especially be informed that some screening assessments need to be done in order to decide if eligibility criteria are met.

- Explanation of the trial (risk/benefit) to the patients (60-120 min). Patient information is handed out in writing.
- Checking of all in- and exclusion criteria (10 min)
- Evaluation of the patient's medical history (10 min)

If inclusion and exclusion criteria are met as far as can be ascertained so far, and if at least 24 h have passed since patient information was given, written informed consent is signed by the participant and the PI. Then the following baseline assessments are performed:

- Pregnancy test for female patients with childbearing potential (blood test hCG).
- Clinical assessment (including physical medical and neurological exam, height and weight).
- Vital signs
- MoCA (20 min)
- Full lab tests

If all inclusion and exclusion criteria are still met, the patient is included in the trial, otherwise a screening failure is declared.

